### Randomisation

Prior to the Cogmed start-up session , the child will be randomised to either the adaptive working memory training program (intervention) group or the non-adaptive working memory training program (placebo) group in a 1:1 ratio. A biostatistician who is independent of the study will generate the randomisation schedule using block randomisation with variable block sizes. Randomisation will be stratified by singleton versus multiple births (twins/triplets) and ‘low’ versus ‘age-typical’ working memory capacity at baseline (total of 4 strata), to ensure equal allocation of these factors across the 2 treatment arms. For this trial, “low” working memory capacity will be classified as performing less than or equal to the 20th percentile on the Backward Digit Recall subtest from the Working Memory Test Battery for Children (WMTB-C) [63]. Approximately 40% of participants will be classified as ‘low’ working memory, based on recently published data from a 7 year follow-up study carried out by the Victorian Infant Brain Studies (VIBeS) group [64]. Twins and triplets (approximately 23%) will be allocated to the same intervention group to reduce contamination.

Randomisation will be conducted via opaque envelopes managed by the project co-ordinator and research assistant. Participants will be allocated the next available sequential study number in the required strata and this corresponds to an envelope which will contain the allocation to intervention or placebo group. The project co-ordinator or research assistant will open the envelope to obtain the treatment allocation either on the morning of the Cogmed start-up session or the night before, depending on the time and location of the session. The participant and their family will remain blinded to the assigned treatment allocation throughout the study. Other than the project co-ordinator and research assistant, all other members of the trial team will also remain blinded to treatment allocation throughout the study.

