**Table 1 T1:** **Outcome measures and study time**-**points**

**Outcome measures**			**Time-point**^**#**^			
			**Baseline***	**2 week**	**12 month**	**24 month**
**Academic achievement**	Wide Range Achievement Test-4th edition (WRAT-4)	Child	•	•	•	•
	Academic performance questionnaire	Parent	•	•	•	•
		Teacher	•			•
**Working memory**	Working Memory Test Battery for Children (WMTB-C)	Child	•	•	•	•
	Automated Working Memory Assessment (AWMA)	Child	•	•	•	•
**Attention**	Test of Everyday Attention for Children (TEACh)	Child	•	•	•	•
**Speed of processing**	CogState	Child	•	•	•	•
**General Cognitive ability**	Differential Ability Scale-2nd edition (DAS-II)	Child	•			
**Behaviour**	Strength & Difficulties Questionnaire (SDQ)	Parent	•	•	•	•
		Teacher	•			•
	Behavior Rating Inventory of Executive Function (BRIEF)	Parent	•	•	•	•
		Teacher	•			•
	Cogmed Training Evaluation Scales	Parent	•	•		
**Motivation**	Intrinsic Motivation Scale	Child	•			
	Intrinsic Motivation Inventory	Child		•		
**Neuroimaging**	MRI	Child	•	•		

^#^The presence of the ‘•’ symbol in Table 1 indicates when an outcome measure will be collected at a specific time-point from either a child or parent/teacher.

^*^Neuropsychological measures and behavioural questionnaires at the baseline time-point were completed prior to enrolment into the trial as part of a regional follow-up program.

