### Sample size

All 221 children from the VICS cohort will be invited to participate in the trial providing that they fit the eligibility criteria for this study. We conservatively estimate that approximately 60% of the VICS cohort will be eligible and will consent to participate in the trial, which will provide a sample size of 126 for this study (63 per treatment group; Figure 2). A participation rate of 60% allows for children who will not be seen through the VICS follow-up (10%), as well as children who do not meet the eligibility criteria (5%; approximately n= 11). A sample size of 63 in each group will enable us to detect an increase in our primary outcome, academic functioning (such as mathematics) 24 months' post-intervention, of 0.5 SD in the intervention compared with the placebo group, with 80% power and a type-I error rate of 5%. An increase of 0.5 SD in academic outcomes is the improvement seen following Cogmed in other populations after 6 months and would be a clinically important difference to detect [39]. Of the 126 participants, we expect approximately 80% to consent to the neuroimaging component of the study, thus a sample size of 100 (50 per group) to assess the secondary objective regarding neuroplasticity. A sample size of 50 in each group with neuroimaging data will enable us to detect differences of 0.57 SD in measures of neuroplasticity (i.e. percentage BOLD signal change between pre-intervention and 2-weeks’ post-intervention for fMRI analyses, and tract volume, FA or AD for DWI analyses), with 80% power and a type-I error rate of 5%.

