### Statistical analysis

All analyses will be carried out using an intention-to-treat approach, including all participants as randomised. Analysis will be carried out on those with outcome data available. Summaries of all primary and secondary outcomes will be presented by treatment group. Results will be presented as means and SDs of age standardised scores for continuous outcomes, and numbers and proportions for categorical variables. Differences between the groups on continuous outcomes will be assessed using linear regression adjusted for stratification factors of multiple births and low/normal working memory capacity at baseline. Models will be fitted using generalised estimating equations (GEEs) to allow for clustering of multiples, with results presented as the mean difference and 95% confidence intervals (CIs) calculated from sandwich estimates of standard errors. As a sensitivity analysis, results will also be adjusted for any other baseline factors where there is a chance imbalance between the 2 groups using linear regression. Differences between groups on binary outcomes will be assessed using logistic regression adjusted for stratification factors of multiple births and low/normal working memory capacity at baseline, again fitted using GEEs. Results will be presented as odds ratios (ORs) and 95% CIs calculated using sandwich estimates of standard errors. Due to the issues of multiple testing, results will be interpreted according to magnitude of the group difference rather than relying solely on significance levels. Compliance and motivation data will be presented descriptively by treatment arm.

For the fMRI data, the effects of group, time (pre-intervention and 2 weeks’ post-intervention) and task (0-back and 1-back conditions) will be examined using factorial analyses by fitting an analysis of variance (ANOVA) model [81]. fMRI effective connectivity will be examined using Dynamic Causal Modelling [82].

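### The only covariate sensitivity analysis picks its covariates by observed baseline imbalance, so they are settled after the arms are compared and not for prognosis

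*Protocol article*

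**What the plan says.** The Statistical analysis section sets the main comparison for continuous outcomes as "linear regression adjusted for stratification factors of multiple births and low/normal working memory capacity at baseline", fitted by GEE to allow for clustering of multiples, with sandwich standard errors. It then adds a sensitivity analysis in which "results will also be adjusted for any other baseline factors where there is a chance imbalance between the 2 groups using linear regression". No other covariate-adjusted analysis is described. The sentence names no candidate factors, no threshold for imbalance and no prognostic criterion.

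The Randomisation section sets 1:1 allocation. Table 1 marks WRAT-4, the primary outcome instrument, at baseline and at every follow-up, and DAS-II at baseline. Its footnote says the baseline neuropsychological measures were completed before enrolment. Neither baseline WRAT-4 nor DAS-II is a named covariate in any model.

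**The concern.** In a randomised comparison every baseline difference is chance, as the protocol's own wording concedes. The size of that difference carries no information on whether the factor predicts 24-month WRAT-4. A rule that selects on it can leave out the strongest predictor because it is balanced, and bring in an irrelevant factor because it is not. The covariate set also cannot be known until the arms have been compared, so the choice stays open at the point where it should be closed.

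What is at stake is the value of the robustness check. Its test does not run at its nominal level, and it usually forgoes the precision that a prognostic baseline measure already in hand would give.

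**Working it through.** **1. The plan's own figure.** Inputs from Sample size: 0.5 SD, 80% power, 5% type I error (taken as two-sided), 63 per group.
- n = 2(1.96 + 0.8416)² / 0.5² = 62.8, so 63 per group.
- Power = Φ(0.5 × √(63/2) − 1.96) = Φ(2.806 − 1.96) = 0.80.

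The stated figure reproduces.

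**2. How often the rule picks something, and what.** The documents give no threshold and no number of factors. Assume 12 independent factors, one of them prognostic. The standard error of a standardised baseline difference is √(2/63) = 0.178.
- p<0.05 rule: the chance that at least one is flagged is 1 − 0.95¹² = 0.46; the prognostic one is flagged in 5%.
- 0.25 SD rule: 0.25/0.178 = 1.40, two-sided probability 0.16. At least one is flagged with probability 1 − 0.84¹² ≈ 0.88; the prognostic one is flagged in 16%.

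**3. Power if one prognostic covariate is always included.** Power = Φ(2.806/√(1 − r²) − 1.96), with r the assumed correlation with the outcome.
- r = 0.5: 2.806/0.866 = 3.24; Φ(1.28) = 0.90.
- r = 0.7: 2.806/0.714 = 3.93; Φ(1.97) = 0.98.

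Simulation gives 0.89 and 0.97-0.98. The correlations are assumptions. For scale, the Background cites correlations of 0.42 to 0.61 between verbal working memory and attainment in very preterm children.

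**4. Simulated trials, 63 v 63.** Ordinary least squares, with strata and sibling clustering left out.

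| Setting | Type I error under the rule (nominal 5%) | Power at 0.5 SD, rule | Power, prespecified |
|---|---|---|---|
| Independent factors, one prognostic (r 0.5-0.7) | about 2.4-4.4% | about 80-83% | 89-97% |
| Correlated factors (0.5), all prognostic (r 0.5-0.7) | about 3-7% | about 88-92% | 97-98% |

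The power columns refer to the p<0.05 and 0.25 SD rules. A looser 0.2 SD rule recovers more power (about 85-88% with independent factors at R² 0.50). In the re-derivation with independent factors, prespecified adjustment held type I error at 4.8-5.5%, nominal within simulation error.

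**5. What the rule does when the prognostic factor is imbalanced.** Take r = 0.7 and the p<0.05 rule. The mean absolute z beyond 1.96 is 2 × 0.0584/0.05 = 2.34, so the mean imbalance is 2.34 × 0.178 = 0.42 SD. The unadjusted estimate is then off by 0.7 × 0.42 = 0.29 SD on average. In simulation, false positives in those trials are 33% unadjusted and about 4% after the rule's adjustment. Power in those trials rises from 54% to 96%. The rule works there, but those are 5% of trials.

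**The case against.** Several points on the other side stand.
- Only a sensitivity analysis is affected. The main model is prespecified, and the protocol says results will be read by magnitude and not by significance alone, so a shift in a nominal 5% level here has limited weight.
- The analysis has a legitimate purpose, to show whether a visible baseline difference drives the result, and step 5 shows that it serves it. A reader might infer that it cannot confirm or challenge the primary result; that goes too far.
- The large power contrast partly argues for a prognostic covariate in general. It depends on the assumed correlation and shrinks when baseline factors are related, as a cognitive battery's would be.

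Three other readings are tempting and not supported.
- One is that the rule materially inflates false positives. With independent factors the departure is conservative; only with correlated prognostic factors does it range either side of 5%.
- It is equally wrong to call the rule conservative in general, or to say it brings almost no precision.
- The third is that the words linear regression in this sentence drop the GEE and treat siblings as independent. The same section calls the main model linear regression too and then says models are fitted by GEE. The natural reading is that covariates are added to that model.

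It may also be said that an unseen SAP could supply the detail. A SAP could name candidate factors and a threshold, but under this sentence it would still select on imbalance. The point concerns a rule the protocol states, not a missing detail.

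**Conclusion.** The point holds as a modest one. The stated rule chooses covariates by chance difference and after the arms are compared, while the baseline measure of the primary outcome is available and unused unless it happens to differ. The selection flaw needs no numerical assumption. The sizes in step 4 do: they rest on the assumed outcome correlations, the number and independence of the factors screened, and the imbalance threshold. They are illustrations, not bounds. The primary estimate, its error rate and the 126-child sample size are untouched.

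**What to change.** Replace the sentence with a sensitivity analysis that adds a short list of prognostic covariates, named before unblinding, to the same GEE model with sandwich errors. Baseline WRAT-4 score should come first, with DAS-II general cognitive ability and continuous Backward Digit Recall as options. Use the logistic GEE in the same way for binary outcomes. Describe baseline differences between arms, but do not use them to select covariates.

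The cost is a change of wording. All these measures are already collected at baseline, and the sample size does not change. The small downside is that an unlisted factor that turns out to be imbalanced can enter only as a labelled post hoc analysis.

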
**Figure 1 F1:**
[figure not shown]
A schematic example of the A) 0-back and B) 1-back conditions of the n-back task.

Children will be carefully instructed about the imaging process prior to the MRI scan, and will have the opportunity to practice the fMRI task during a simulated ‘mock’ MRI session, which will occur prior to the scan on the same day. This preparation process will be conducted by experienced research staff and allows children to familiarise themselves with the scanner and scanning process, and raise any concerns they may have prior to the MRI scan. Furthermore, this process assists with identifying children who are unlikely to comply with the MRI procedure and is important for the acquisition of good quality MRI images without the use of sedation.

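### The fMRI ANOVA omits the sibling clustering and strata adjustment used for the trial's other outcomes, and the 0.57 SD detectable difference treats imaging consent as complete scan data

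*Protocol article*

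**What the plan says.** The Statistical analysis section of the protocol article first sets a general model. Group differences on continuous outcomes come from linear regression, and those on binary outcomes from logistic regression. Both are adjusted for multiple birth and baseline working memory level, and both are fitted by GEE with sandwich standard errors so that children from one family are not counted as independent. A separate paragraph then deals with fMRI: the effects of group, time and task "will be examined using factorial analyses by fitting an analysis of variance (ANOVA) model". It mentions no family term and no stratification factor.

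The Randomisation section states: "Twins and triplets (approximately 23%) will be allocated to the same intervention group to reduce contamination".

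The Sample size section says of the 126 participants that "we expect approximately 80% to consent to the neuroimaging component of the study, thus a sample size of 100 (50 per group"). It continues: "A sample size of 50 in each group with neuroimaging data will enable us to detect differences of 0.57 SD". For fMRI the measure is "percentage BOLD signal change between pre-intervention and" the scan two weeks after training. The MRI preparation text after Figure 1 says that the mock session "assists with identifying children who are unlikely to comply with the MRI procedure", and that scanning is done without sedation.

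**The concern.** The reason for using GEE elsewhere applies equally to the imaging sample. Siblings are allocated together, so any correlation between their BOLD changes inflates the variance of the between-group comparison. A model that ignores this gives standard errors that are too small. The fMRI paragraph also does not say which term carries the treatment effect: group-by-time, or group-by-time-by-task.

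The power statement has a separate weakness. It goes straight from the number consenting to the number with data. A pre-to-post change exists only for a child with two usable scans, separated by a training period of up to seven weeks plus two more. The mock session takes place on the day of the scan, after consent, so a child found unable to comply is lost from within the 100. The analysis is limited to children with outcome data, so such losses reduce the analysed number directly.

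At stake is how the neuroplasticity objective is read. A borderline positive result would be slightly too easy to obtain. A null result would be judged against a sensitivity that the trial may not have.

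**Working it through.** **Inputs from the protocol article.** 126 participants, 80% imaging consent, 50 per group, 0.57 SD, 80% power, 5% type I error (Sample size); 1:1 allocation, about 23% multiples, siblings in the same arm (Randomisation).

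**Inputs assumed, because the article gives none.** Correlation between siblings' BOLD changes of 0.3 to 0.7; each multiple has exactly one co-sibling who is also scanned; 10% to 30% of scan pairs unusable.

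**Step 1: reproduce the stated figure.** 126 × 0.80 = 100.8, taken as 100, or 50 per group. For two independent means, two-sided 5%, 80% power:

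- Normal approximation: (1.960 + 0.842) × √(2/50) = 0.560 SD.
- Noncentral t: 0.566 SD, which rounds to 0.57.

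A one-sided test would give 0.497 SD, so the figure is two-sided. It reproduces only with all 50 per group analysed and no design effect, that is, with no scan loss and independent children.

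**Step 2: sibling clustering and the type I error.** With a share of 0.23 in pairs, the design effect is DE = 1 + 0.23ρ. A test that ignores it has true size 2 × [1 − Φ(1.96/√DE)].

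| ρ (assumed) | DE | True size of a nominal 5% test | Effective n per arm, 50/DE | Detectable difference (noncentral t) |
|---|---|---|---|---|
| 0.3 | 1.069 | 5.8% | 46.8 | 0.585 SD |
| 0.5 | 1.115 | 6.3% | 44.8 | 0.598 SD |
| 0.7 | 1.161 | 6.9% | 43.1 | 0.611 SD |

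The third column takes the within-child correlation as correctly handled. The last column is the power statement corrected for clustering alone, with no scan loss.

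**Step 3: scan loss alone (noncentral t).** Consenters needed = 100/(1 − loss), rounded up.

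| Pairs lost (assumed) | n per arm | Detectable difference | Power at 0.57 SD | Consenters needed for 100 pairs |
|---|---|---|---|---|
| 0% | 50 | 0.566 SD | 81% | 100 |
| 10% | 45 | 0.597 SD | 76% | 112 |
| 20% | 40 | 0.634 SD | 71% | 125 |
| 30% | 35 | 0.679 SD | 65% | 143 |

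At 20% loss, 125 of the 126 participants would have to consent. At 30% the requirement exceeds the trial.

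**Step 4: both together.** With 20% loss and ρ = 0.5, the effective n is 40/1.115 = 35.9 per arm and the detectable difference is about 0.67 SD.

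**The case against.** Several stronger readings are tempting, and the article does not support them.

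- *A reader might infer that the ANOVA is not the analysis that was powered.* With two time points and time treated as within-child, the group-by-time test averaged over task is the same as comparing per-child change between groups (F = t²). The Sample size and Statistical analysis sections agree on this.
- *A reader might infer that the four cells per child (two times, two tasks) are treated as independent*, which would overstate the variance of the group-by-time contrast by 1/(1 − r), or 1.4 to 3.3 times for r = 0.3 to 0.7. The text never says so. Time and task both vary within child, so a within-child analysis is the natural reading. Nor could this stand beside the type I figures above. Even at r = 0.3 the overstatement (1.43) would outweigh the largest design effect in Step 2 (1.16) and make the test conservative.
- *A reader might infer that the diffusion measures share the gap.* No separate model is given for tract volume, FA or AD, so the general GEE regression covers them.
- *A reader might infer that 0.57 SD certainly cannot be reached.* The statement is conditional on 50 per group having data, and the article gives no failure rate. The loss figures are assumptions.

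Other objections stand in part. The clustering effect is small. Broken sibling pairs in the imaging subset would shrink it, while triplets would enlarge it. Leaving out the stratification factors costs precision rather than causing bias, and stable level differences between strata cancel from a change score. A condensed article may leave error-structure detail to a fuller plan. The article also says results will be read by magnitude and not by significance alone, which tempers over-reading of a null.

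None of this removes the two core facts: the article sets a specific fMRI model that omits the trial's own safeguards, and its power statement removes nothing between consent and data.

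**Conclusion.** The point holds in two limited parts. First, the fMRI model as stated does not account for siblings or strata. The size is modest: about 5.8% to 6.9% against a nominal 5%, conditional on assumed sibling correlations of 0.3 to 0.7 and one scanned co-sibling per multiple. The omission is read from the effects listed; the article does not say outright that clustering will be ignored. Second, the 0.57 SD is arithmetically correct but rests on complete scan pairs from every consenting child and on independence. Scan loss is the larger of the two effects: 0.60 to 0.68 SD, with power at 0.57 SD of 76% to 65%, for an assumed 10% to 30% loss. Both parts concern a secondary objective, but both are worth correcting because the correction is cheap.

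**What to change.** Keep time and task as within-child factors. Name group-by-time, and group-by-time-by-task if it is intended, as the treatment effect. Fit it with the trial's own family-clustered GEE, sandwich errors and adjustment for the two strata, for example on per-child change or on baseline-adjusted post-training values by region. No change is needed for the diffusion measures.

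In the Sample size section, state how many children are expected to have two usable scans and give the detectable difference for that number, allowing for sibling clustering.

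The cost is slightly more analysis work and one less favourable stated figure. No extra scans or participants are required.

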### Consent

Written informed consent was obtained from the participant’s parent or guardian for the publication of this manuscript and any accompanying images.

## Discussion

As the number of EPT/ELBW survivors has increased, the focus of research into preterm birth has shifted to improving long-term outcome of these children. Because EPT/ELBW children are at a greater risk of poor educational, behavioural and social outcomes than their term-born counterparts, implementation of evidence-based interventions are crucial for reducing the risk of long-term impairment in these children. Early academic underachievement can hinder later life success and job attainment, which results in additional economic and societal burden. Working memory deficits have been associated with poor school performance, both of which are exhibited by preterm children [17,22,23,25]. Emerging evidence suggests that a training intervention in the early school period can improve working memory and may in time enhance academic outcomes in term-born children. A priority now is to establish whether this potentially promising intervention can lead either to immediate impacts on working memory capacity or, more importantly, to long-term improvements in important functional outcomes such as academic skills in preterm children.

The proposed study will be the first study to investigate the effectiveness of Cogmed, an adaptive working memory training program, in the extremely preterm population within a controlled environment and assess whether improved working memory generalises to improving academic outcomes 24 months’ post-intervention. Furthermore, the incorporation of a range of advanced MRI techniques in this RCT of Cogmed is novel, and will be essential for determining and monitoring the neural changes that occur as a result of adaptive working memory training.

If effective, the Cogmed program could potentially serve as a valuable intervention for improving educational outcomes in EPT/ELBW children. In summary, this trial has the potential to provide an evidence base for a promising, new intervention for improving academic and developmental outcomes in EPT/ELBW children and will contribute to the existing literature surrounding the efficacy of Cogmed.

